### Glycosylated haemoglobin (HbA1c) and fasting blood sugar

HbA1c and fasting blood sugar will be measured at baseline and at 60 days from randomisation. This will enable determination of the frequency of undiagnosed diabetes in those presenting with TBM, assess diabetic control in those known to have diabetes, and evaluate the influence of dexamethasone and anti-tuberculosis treatment on diabetic control over the first 60 days of TBM treatment. To enable more detailed phenotyping of diabetes we will also measure C-peptide and blood lipids at baseline and store plasma for future diabetes related auto-antibody testing.

### Strongyloides

All enrolled participants will be tested for serological evidence of Strongyloides infection (past or latent infection) with stool examination for evidence of active infection at baseline and at 60 days from randomisation. When infection is detected, treatment with ivermectin will be provided. High-dose corticosteroids can lead to re-activation of latent Strongyloides and hyperinfection syndrome. Stool will be examined for Strongyloides larvae on day 60 (end of study drug) to determine whether reactivation alters TBM treatment responses.

### Synacthen test

We will compare adrenal responsiveness at 3 weeks after randomisation and at the end of study drug treatment (6 or 8 weeks depending upon disease severity) in 100 consecutive patients using the short Synacthen test. The patient’s background cortisol level is measured by drawing 2mls of blood at 0900hrs. 250mcg of Synacthen is then administered intravenously; 3ml samples of blood are taken at thirty minutes and sixty minutes to measure the cortisol level after this adrenal stimulation. Synacthen test will be repeated at day 60 after randomisation.

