### Dexamethasone induced adrenal suppression

Iatrogenic administration of exogenous corticosteroids is associated with adrenal suppression, and the sudden cessation of treatment can lead to Addisonian crises which can be life-threatening. For this reason it is common practice to prescribe corticosteroids in tapering doses, to allow recovery of the adrenal cortex during the treatment period. Thus, by the time the corticosteroid is finished, normal endogenous cortisol production will have resumed with no risk of Addisonian crisis. Whether the use of corticosteroids in the doses prescribed in infectious diseases are associated with significant adrenal suppression is not clear and has not been investigated.

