## Trial management

### Interventions

All participants will receive the standard of care anti-TB drugs and ART drugs according to respective national guidelines. In ART-naive patients, ARTs will be started 6–8 weeks after the start of anti-tuberculosis drugs. Study participants for the main trial will be randomised to receive either dexamethasone or placebo (investigational medicinal product (IMP)) as an extra medication for 6–8 weeks, dependent upon the severity of TBM disease (
Table 2). Dexamethasone/placebo will be dispensed at randomisation from the site pharmacy in intravenous and oral (tablet) formulations. Placebo will be identical in appearance to active drug and dosed and dispensed in the same way. The study drug will be given to participants as early as possible in the treatment of TBM but no later than 7 days from the start of anti-tuberculosis treatment.

**Table 2. T2:** Study drug treatment regimen following randomisation.

	MRC Grade I Daily dexamethasone dose/route	MRC Grades II and III Daily dexamethasone dose/route
Week 1	0.3 mg/kg/24 hrs IV	0.4 mg/kg/24 hrs IV
Week 2	0.2 mg/kg/24 hrs IV	0.3 mg/kg/24 hrs IV
Week 3	0.1 mg/kg/24 hrs IV	0.2 mg/kg/24 hrs IV
Week 4	3mg/24 hrs oral	0.1 mg/kg/24 hrs IV
Week 5	2mg/24 hrs oral	4 mg/24 hrs oral
Week 6	1 mg/24 hrs oral	3 mg/24 hrs oral
Week 7	Stop	2 mg/24 hrs oral
Week 8		1 mg/24 hrs oral

Participants for the DILI strategy study will be randomised to one of three strategies (
Figure 2): Strategies are as follows:

1)Observe: measure transaminases, bilirubin, and INR every 3 days; do not change/stop anti-tuberculosis drugs unless transaminases rise to ≥10x normal, or total bilirubin rises >2.5mg/dl (>43 µmol/L), or INR >1.5 or symptoms of hepatitis worsen (nausea, vomiting, abdominal pain), in which case go to Strategy 3.2)Stop pyrazinamide (Z) alone. Observe, measuring transaminases, bilirubin, and INR every 3 days. If transaminases do not fall to <5x ULN by day 5, or total bilirubin rises >2.5mg/dl (>43 µmol/L), or INR >1.5 or symptoms of hepatitis worsen at any time (nausea, vomiting, abdominal pain), go to Strategy 3.3)Current standard of care (current US CDC guidelines
^4^,
Supplementary File 3).

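### The text plans a Synacthen test at the end of study drug, but Table 3 schedules only day 21 and day 60, and day 60 is about 18 days (grade I) or 4 days (grades II and III) after the planned last dose

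*Protocol article*

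**What the plan says.** Four places in the protocol article bear on the timing of the later Synacthen test.

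- *Synacthen test* (Data collection): adrenal responsiveness is compared at 3 weeks and "at the end of study drug treatment (6 or 8 weeks depending upon disease severity", in 100 patients taken consecutively. The same paragraph closes with: "Synacthen test will be repeated at day 60 after randomisation".
- *Table 3* (assessment schedule): the Synacthen row carries two marks, one for day 21 and one in the day 60 column. The table has no week 6 or week 8 column.
- *Strongyloides* (Data collection): "Stool will be examined for Strongyloides larvae on day 60 (end of study drug". The equation of day 60 with end of drug is made for all participants, whatever their grade.
- *Table 2* (Interventions; "Study drug treatment regimen following randomisation"): grade I has six weekly dose steps and stops at week 7; grades II and III have eight weekly steps.

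The background section on dexamethasone-induced adrenal suppression gives the reason for the study. Tapering is used "to allow recovery of the adrenal cortex during the treatment period", while the significance of suppression at the doses used in infectious diseases "is not clear and has not been investigated".

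**The concern.** The text defines the adrenal comparison by a test at the end of the allocated course. A site that follows Table 3 would not do that test at that time: it would test on day 21, on drug, and on day 60, when the planned course is normally over.

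A test some time after the last dose measures adrenal function after a period of recovery. It cannot show whether function had returned by the moment the drug stopped, which is what the background section says tapering achieves. The drug-free interval at day 60 also depends on MRC grade, because grade sets the length of the course. Results from grade I and from grades II and III would therefore be taken at different points of recovery. A test missed at the end of the course cannot be recovered later.

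**Working it through.** **Inputs.** Table 2: six weekly steps (grade I), eight weekly steps (grades II and III). Table 3 and the Synacthen section: later test on day 60 after randomisation.

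**The plan's own figure.** Weekly steps × 7: 6 × 7 = 42 days and 8 × 7 = 56 days. This reproduces the stated 6 or 8 weeks.

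**Gap at day 60** = 60 − last dosing day. The interval from randomisation to first dose is not fixed: the limit of "no later than 7 days from the start of anti-tuberculosis treatment" is counted from anti-tuberculosis treatment, not from randomisation. The delays below are therefore assumptions.

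| Assumption on first dose | Grade I | Grades II and III | Difference |
|---|---|---|---|
| Day 0 (last dosing day 41 / 55) | 60 − 41 = 19 | 60 − 55 = 5 | 14 |
| Day 1 (last dosing day 42 / 56) | 60 − 42 = 18 | 60 − 56 = 4 | 14 |
| 1 to 3 days later than that | 17 to 15 | 3 to 1 | 14 |
| 7 days later (extreme) | 11 | −3 (still on drug) | 14 |

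The gap in grade I is substantial in every row. In grades II and III it is small, and a delay of four days or more would close it. The 14-day difference between grade groups does not depend on the assumption.

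**Is the Table 3 column read correctly?** The brain MRI row, laid out in the same way, falls on day 0, day 60 and month 12. That agrees with the Imaging section, so the Synacthen mark in the same column is day 60.

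**Two readings of the Synacthen paragraph.**

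1. Day 60 stands for the end-of-drug test. The test is then mistimed against Table 2.
2. Day 60 is a third test. The end-of-drug test is then missing from Table 3.

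On either reading, following the schedule does not deliver the stated comparison.

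**Who is concerned.** Allocation is 1:1, so about 100 × 0.5 = 50 of the 100 receive dexamethasone. The article gives no grade I share. If it were 30% to 40% (an assumption), 50 × 0.30 = 15 to 50 × 0.40 = 20 dexamethasone patients would be tested about two and a half weeks after their last dose. Each 10 percentage points of grade I share corresponds to 5 such patients.

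**The case against.** The strongest reply is that the paragraph names three tests, so the end-of-drug test exists and Table 3 merely leaves it out; the full protocol may carry the detail. That reading is possible. It moves the fault from the text to the schedule but does not remove it, because the article's own text and table disagree.

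It can also be said that the main open question is whether these doses suppress the adrenals at all. The day 21 test addresses that, since both grade groups are still on drug then. This stands, and it limits the point to the later test. It also stands that 4 days in grades II and III lies within the ±7-day windows that the article allows for outpatient review and day 60 imaging. The practical weight is in grade I.

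Four stronger conclusions might be inferred, and the documents do not support them.

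- *Suppression will be underestimated.* This is plausible if function recovers off drug, but the article gives no recovery rate or cortisol data.
- *The treatment comparison is confounded with grade.* Randomisation is stratified by MRC grade and the ancillary studies are analysed by allocated arm, so dexamethasone versus placebo at day 60 is a fair comparison of that day.
- *All 100 participants are affected.* About half take placebo and have no steroid-free interval.
- *The day 60 fasting glucose has the same fault.* The section on HbA1c and fasting blood sugar sets its aim over the first 60 days, which day 60 matches.

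**Conclusion.** The inconsistency is real and minor. Day 60 is about 18 days after the planned last dose in grade I and about 4 days in grades II and III, assuming that study drug starts promptly after randomisation and the Table 2 course is completed. It should not be reported as an end-of-treatment result, and "on day 60 (end of study drug" does not agree with Table 2.

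What is affected is the change from day 21 to end of drug, and any comparison between grade groups, because the drug-free interval differs by 14 days. Whether suppression at the end of the course would be missed, and in how many, cannot be computed from the article. The matter is confined to one ancillary study at one hospital and leaves the primary endpoint, the sample size and the main analysis untouched.

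**What to change.** Reconcile Table 2, Table 3, the Synacthen section and the Strongyloides section. State whether the later Synacthen test is at end of study drug, at day 60, or both, and make Table 3 match the end-of-drug comparison that the text describes.

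If only day 60 is kept, correct the end-of-drug label, describe the test as a post-treatment recovery test, and account for days since last dose and MRC grade in the analysis. Among patients who complete the course, these two variables nearly coincide, so a model cannot separate them. Results should therefore also be shown by grade group.

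The cost is a schedule and wording edit. An end-of-drug test may need a visit near week 6 for grade I patients. Keeping both time points would add one test per patient to the two now in Table 3.

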### Lumbar puncture

Lumbar puncture should be performed, unless clinically contraindicated, as part of routine clinical care for the baseline assessment and on days 30 and 60 after randomisation to assess treatment response. Day 60 lumbar punctures are not routine practice in the Jakarta hospitals and will therefore not be mandated by the trial in these centres. Opening pressure should be measured, at least 5mls of CSF should be taken for mycobacterial investigations alone, and assessments of cell count and differential, protein, glucose (paired with serum), and lactate should also be performed on 1–2 mls of additional CSF. Ziehl Neelsen (ZN) stain, GeneXpert, and
*M. tuberculosis* culture will be performed on all CSF taken. As part of an ancillary study of the impact of dexamethasone on CSF inflammation and gross cerebral pathology we will measure concentrations of a variety of inflammatory mediators in the CSF (leucocytes, cytokines, chemokines, and eicosanoids, for example) at baseline and on days 30 and 60 after randomisation to determine how dexamethasone influences their expression.

### Hyponatraemia and raised intracranial pressure

In the subset of participants enrolled to HTD, Ho Chi Minh City, Vietnam, we will investigate the pathophysiology of TBM-associated hyponatraemia by serial assessments of fluid balance, paired plasma and urinary sodium and osmolality, and intravascular volume by Doppler ultrasound assessment of inferior vena cava collapsibility index
^18,
19^. We will also use portable ultrasound to measure the optic nerve sheath diameter, which has been shown to be a reliable and non-invasive measure of raised intracranial pressure
^20,
21^. These additional measurements will be assessed at days 0, 3, and 7, and weekly until discharge. Plasma cortisol will be measured at day 0.

### Imaging

Chest Xray will be performed at screening and on day 60 and 12 months after randomisation. In the subset of participants enrolled to HTD, Ho Chi Minh City, Vietnam, we will perform brain imaging by MRI (or CT if the participant cannot tolerate an MRI) at baseline (+/- 7 days) and at 60 days (+/- 7 days) and at 12 months (-0/+1 month). At sites other than HTD, Ho Chi Minh City, Vietnam, brain imaging is performed based upon the routine care at that site. Brain imaging may not always be readily available, and this study does not mandate brain imaging for every patient. Brain imaging for suspected TBM is strongly supported, and individual decisions will be made by the treating physician.

## Adverse events and safety reporting

### Adverse events

Specific procedures will be followed when notifying and reporting adverse events (AEs) or adverse reactions (ARs). The definitions of the EU Directive 2001/20/EC Article 2 based on the principles of ICH good clinical practice (GCP) apply to this trial protocol. All AEs and ARs will be assessed as to whether they are serious or not. If the event is serious and not only related to TBM, or is fatal, then a serious adverse event (SAE) form must be completed and the OUCRU CTU notified within 24 hours. All AEs and ARs (serious and non-serious) should be graded using toxicity gradings.

Causality of all SAEs or serious adverse reactions (SARs) in relation to the trial therapy (dexamethasone) will be assessed. There are five categories: unrelated, unlikely, possible, probable, and definitely, related. If the causality assessment is unrelated or unlikely to be related, the event is classified as an SAE. If the causality is assessed as possible, probable or definitely related, then the event is classified as an SAR. If there is at least a possible involvement of the trial treatment (or comparator), the investigator must assess the expectedness of the event. An unexpected adverse reaction is one not previously reported in the current Summary of Product Characteristics (SPC) at the time the event occurred, or one that is more frequent or more severe than previously reported. If a SAR is assessed as being unexpected, it becomes a suspected unexpected serious adverse reaction (SUSAR). Investigators should always check the current version of the SPC.

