### Use of adjunctive dexamethasone

How corticosteroids confer a survival benefit, and whether they do so in HIV-infected patients with TBM, remains uncertain. In TBM dexamethasone may reduce the early intracerebral inflammatory response, prevent hydrocephalus infarction and tuberculoma formation, and reduce the incidence of neurological IRIS. Dexamethasone may reduce the risk of DILI and thereby improve outcome by enabling uninterrupted anti-tuberculosis treatment. The current evidence-base for using adjunctive corticosteroids for the treatment of HIV-associated TBM is restricted to 98 adults recruited to a trial in Vietnam
^8,
13^. This trial randomised a total of 545 subjects (98 of them HIV-positive) and reported an overall reduction in 9-month mortality due to dexamethasone from 41.3% (112/271) to 31.8% (87/274) (hazard ratio of time to death 0.69; 95% confidence interval (CI) 0.52–0.92, P=0.01). While there was no clear evidence of treatment effect heterogeneity according to HIV status, the number of included HIV-infected subjects was low and the observed benefit in that subgroup was smaller: 61.4% (27/44) in the dexamethasone group died, compared to 68.5% (37/54) in the placebo group (hazard ratio of time to death 0.86; 95% CI 0.52–1.41; P=0.55). On the basis of these data most international guidelines cautiously recommend dexamethasone should be given for HIV-associated TBM, but all acknowledge the paucity of evidence and the need for additional controlled trial data.

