### Secondary endpoints – ACT HIV (main trial)

The secondary endpoints of the main trial are as follows:

a)Neurological disability at day 30 from randomisation, monthly until completion of anti-tuberculous drugs, and at months 12, 18 and 24. The main endpoint is the 12-month assessment and subjects who died before 12 months will be treated as having a score of 6 (‘dead’). Neurological disability will be assessed by the modified Rankin score (
Table 1).b)Time to first new neurological event or death during a follow-up period of 12 months. A neurological event is defined as a fall in Glasgow Coma Score (GCS) by ≥2 points for ≥2 days from the highest previously recorded GCS (including baseline), or the onset of any of the following clinical adverse events: cerebellar symptoms, focal neurological signs, or seizures.c)Time to neurological IRIS events from randomisation until 6 months. We will follow the International Network for the Study of HIV associated IRIS (INSHI) case definition of IRIS (
14,
Supplementary File 2). Rate of neurological IRIS is defined as the number of IRIS events divided by the observed person-time of follow-up in each treatment group. d)Time to new acquired immunodeficiency syndrome (AIDS)-defining event (as per World Health Organisation classification) or death, during a follow up period of 12 months.e)Time to HIV-associated malignancy from randomisation until 12 months. Rate of HIV-associated malignancy is defined as the number of events of the three major HIV-associated malignancies (Kaposi sarcoma, high grade B-cell non-Hodgkin lymphoma and invasive cervical cancer) divided by the observed person-time of follow-up in each treatment group. f)Serious adverse events until 12 months. Comparison of the frequency of serious adverse events between treatment groups will form an important part of the study analysis.g)Endpoints assessed at 24 months of follow up. All participants will continue to be followed up for 24 months and the following outcomes will be reported once this period has been completed for all participants: overall survival until 24 months, neurological disability at 24 months, recurrence of TBM until 24 months, time to new AIDS defining event or death until 24 months, and rate of HIV-related malignancy until 24 months.

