### Clinical assessment

Clinical assessment will include conscious level by GCS, new or ongoing focal neurological deficit, clinical treatment response, all serious adverse events including new malignancies and opportunistic infections, all adverse events of any grade leading to modification of anti-tuberculosis treatment or ART or their interruption/early discontinuation (and clinician-assessed likelihood of relationship of adverse event to dexamethasone), and adherence to drugs (study drug, anti-tuberculosis drugs and ART). Assessment of disability by the modified Rankin score will be performed at day 30 from randomisation, monthly until completion of anti-TB drugs, and at months 12, 18 and 24.

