### Analysis of adverse events

The number of patients with any adverse events and specific events, respectively, will be summarised and informally compared between the two treatment arms based on Fisher’s exact test. The total number of adverse event episodes per patient will also be summarised and informally compared based on a quasi-Poisson regression model with treatment as the only covariate. The following subgroups of adverse events will also be separately summarised: grade 3&4 adverse events; serious adverse events; serious adverse events possibly, probably, or definitely related to the study drug; adverse events leading to TB treatment or ART interruptions. Grade 3&4 laboratory abnormalities will be summarised in the same way as clinical adverse events.

Adverse events due to DILI will be recorded for the DILI study but also for the primary intervention (dexamethasone or placebo). An increased number of adverse events in DILI arms 1 and 2 are not expected, but if they do occur these adverse events will be associated with both the DILI randomisation strategy and for the primary intervention arm in which they occurred.

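### The SAE form is not required for non-fatal serious events attributed to TBM alone, but the SAE endpoint, visit collection and safety reporting carry no such exclusion, so the endpoint may be selective

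*Protocol article*

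**What the plan says.** Under Adverse events, the protocol article first says: "All AEs and ARs will be assessed as to whether they are serious or not". It then states when a form is needed: "If the event is serious and not only related to TBM, or is fatal, then a serious adverse event (SAE) form must be completed". The same sentence requires the trials unit to be told within 24 hours. The form and the rapid notification thus share one filter.

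Elsewhere the filter does not appear:

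- **Secondary endpoints – ACT HIV (main trial), item (f)** makes serious adverse events to 12 months a secondary endpoint: "Comparison of the frequency of serious adverse events between treatment groups will form an important part of the study analysis".
- **Clinical assessment** lists, among what is collected at visits, "all serious adverse events including new malignancies and opportunistic infections".
- **Safety reporting** sends all SAEs to the Oxford ethics committee each year, and to the DMC under its charter.
- **Analysis of adverse events** names, among the subgroups to be summarised by arm, "serious adverse events; serious adverse events possibly, probably, or definitely related to the study drug".

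Use of adjunctive dexamethasone gives the ways in which the drug may act. It may "prevent hydrocephalus infarction and tuberculoma formation, and reduce the incidence of neurological IRIS".

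**The concern.** A filter on rapid notification of expected disease events is ordinary and sensible. Here the same filter also decides whether the form is completed at all, and it rests on the site's judgement of cause. The events filtered out are non-fatal, serious and ascribed to the disease alone. That class overlaps the complications that the protocol expects dexamethasone to change.

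A randomised comparison of serious events is most useful when it does not depend on attribution. If inclusion depends on a judged cause, and treatment alters how often that cause arises, the count can be selective even when every judgement is correct and blinded. At stake is the meaning of a named secondary endpoint and of the SAE information sent to the DMC. Sites also hold two instructions that point different ways, and may record differently.

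**Working it through.** The plan gives no SAE rate, so there is no figure to reproduce. The check sets the sections side by side.

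**1. What the form rule covers.** Serious events fall into three groups:

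| Serious event | Form required under Adverse events? | Within the wording of endpoint (f) and Clinical assessment? |
|---|---|---|
| Fatal, any cause | Yes | Yes |
| Non-fatal, not due to TBM alone (including suspected drug effects) | Yes | Yes |
| Non-fatal, judged due to TBM alone | No | Yes |

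The conflict is confined to the third row.

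**2. Does any section say that endpoint (f) is built from the forms?** No. Nor does any section say that it is built from a wider record. The scope of the endpoint is open.

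**3. Could the third row be recovered from other records?** In part.

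- Endpoint (b) is: "Time to first new neurological event or death during a follow-up period of 12 months". It counts only the first event. Apart from death, it needs a sustained fall in coma score, cerebellar symptoms, focal signs or seizures.
- Endpoint (c) covers neurological IRIS to 6 months only.
- Endpoint (a) records disability at set times, not events.
- Overall survival covers deaths, which always need a form anyway.
- The general adverse event tables are not a sure remedy. Besides serious events, Clinical assessment lists only adverse events that change or interrupt anti-tuberculosis treatment or ART. A serious TBM complication that leaves those drugs unchanged might not be recorded as an adverse event if the site follows the form rule.
- Scheduled serial brain MRI and the detailed hyponatraemia and intracranial pressure measurements are limited to one Vietnamese hospital.

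**4. Where the filter sits.** The five-category causality assessment applies to SAEs. An event already sorted as due to TBM alone triggers no form, so it may not reach that assessment.

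**5. What a forms-only count would leave out.** Write f for the proportion of an arm with at least one event that needs a form. Write t for the proportion whose only serious events are non-fatal and ascribed to TBM alone. Then

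all-SAE difference = (f_dex − f_placebo) + (t_dex − t_placebo).

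A forms-only count reports the first bracket and drops the second. If dexamethasone prevents such complications, the second bracket is negative. If it causes events that are mistaken for TBM, the bracket is positive. If neither happens, it is near zero. For scale, 1:1 allocation gives 520 / 2 = 260 per arm, so each percentage point in that bracket is 260 × 0.01 = 2.6 participants. The documents supply neither f nor t, so the calculation stops there.

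**The case against.** The strongest reply is that the rule governs a form and a notification, not an endpoint. The neighbouring text has every adverse event assessed for seriousness and graded. Clinical assessment collects all serious events, and endpoint (f) and the analysis section carry no exclusion. On that reading nothing is lost. This stands to the extent that the article does not show the endpoint to be incomplete. A reader might infer that these events never enter the SAE count. The documents do not support that, because no section names the forms as the endpoint's only source.

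A reader might also infer that the comparison leans against dexamethasone, with prevented complications invisible and steroid harms counted. That is not supported either. Endpoints (a) to (c) and survival compare many of these complications by arm. An event that the investigator thinks dexamethasone may have caused is not due to TBM alone and needs a form. Only drug-caused events wholly misattributed to TBM would escape. Investigators are blinded, which prevents knowing differential classification. With no SAE rates in the documents, any numerical example of a reversed conclusion would rest on invented inputs.

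The DMC is to receive adverse events by arm under Interim analyses, and its charter is not shown. It therefore cannot be said that its report is limited to the forms.

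Finally, CRF instructions and the derivation of the endpoint may stand in the full protocol or the SAP. Their absence from an article is no fault. What remains is not an absence: the article states a rule that is narrower than the text around it. An analysis plan may not be able to recover events that sites were not required to record.

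**Conclusion.** The concern holds in a limited form. The form rule under Adverse events conflicts with endpoint (f), Clinical assessment, Safety reporting and Analysis of adverse events over one class: non-fatal serious events ascribed to TBM alone. If endpoint (f) is drawn from the forms, it may omit that class, and the contrast between arms could be selective in a way that depends on treatment. If it is drawn from a wider record, sites still have conflicting instructions and the endpoint's scope is unstated.

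The possible selection rests on two things: that the forms feed the endpoint, which is an assumption, and that dexamethasone changes the frequency of these complications, which the protocol puts forward as a possibility. Direction and size cannot be given. The primary endpoint is unaffected.

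**What to change.** Reconcile the sections as follows:

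- Record every serious event, whatever its attributed cause, as Clinical assessment already says.
- Use the judgement that an event is due to TBM alone only to decide whether 24-hour notification is needed.
- Define endpoint (f) as all SAEs irrespective of attribution, with TBM-attributed and other SAEs shown separately by arm.
- Put the same split in the DMC report.

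The cost is some additional CRF entries. The change adds no expedited reports, visits or procedures, and clinical care stays the same.
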